### Measures

#### Primary outcomes: feasibility, acceptability, and appropriateness

We will assess the feasibility, acceptability, and appropriateness of deploying the RAPD implementation strategies using a mixed methods approach: (1) we will conduct semi-structured interviews with the pilot study middle school health teachers at three different time points: pre-implementation, during implementation, and post-implementation of the MMH program. We will conduct these interviews via videoconferencing and record and transcribe them verbatim. Our assessment will focus on the compatibility of delivering the MMH curriculum with RAPD in addressing key barriers (e.g., intervention's capacity to address new drugs) and the perceived fit of MMH within the context regarding appropriateness [86]. (2) We will administer a survey assessing feasibility, acceptability, and appropriateness using items from Weiner et al. [89] during the post-implementation interview. Each construct will use a 5-point Likert scale and consist of four items. For example, participants will rate their agreement on statements such as “RAPD is appealing” and “RAPD seems suitable.” These quantitative measures will provide valuable data to complement the insights gained from the qualitative data.

### Secondary outcomes

#### Fidelity: dose delivered, adherence

We will utilize an existing MMH fidelity tracking form administered at the end of each unit currently used by health teachers to gather data on curriculum use. We will assess the dose delivered by summing the lessons covered during the drug use prevention units (17 lessons). We will assess adherence by examining reports of key functional content areas addressed in the drug use prevention units, such as evaluating the problem, identifying reliable sources of information, and practicing key prevention skills (e.g., refusal skills). We will also use the tracking form to assess adaptations based on the Framework for Reporting Adaptations and Modifications-Enhanced (FRAME), e.g., added content, removed content [90].

#### Teacher self-efficacy and behavioral capability

We will adapt the GSE-6 (General Self-Efficacy Scale) [91] for the context and tailor behavioral capability items using the CDC’s characteristics of effective health education [92] and assess these constructs in semi-structured interviews.

#### Student outcomes

Secondary outcomes at the student level are summarized in Table 2. Student surveys will be administered at baseline (the beginning of the semester or trimester), when the student is in health class, and after delivery of the drug use prevention units (post-test). During the school year, participating teachers will administer the pre-/post surveys for each cohort of students if they teach health for more than one term/year.

**Table 2 Tab2:** Secondary study measures student level

Student-level outcomes			
**Construct (# items)**	**Scaling**	**Timing**	**Source**

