#### Eligibility and randomization

We will focus on schools that could most benefit from RAPD by employing the following screening criteria: schools must include seventh-grade education level; health teachers must report delivering less than 80% of the MMH curriculum (the state-identified fidelity standard) and/or report two or more barriers to MMH implementation (see “Measures”). These criteria are adapted from a previous school-based study and informed by study partners and the study team's previous research on MMH implementation [62, 63]. Five of the matched sites will be randomized to the RAPD and five to standard implementation: the MMH curriculum manual, training, and technical assistance. Research team members will use the GenRandGroups function within the DescTools package (version 0.99.54) in R. The randomization procedure is designed to pilot methods to ensure balanced participant allocation across experimental conditions. Schools will be the randomization unit, with matching criteria for assigning schools to treatment groups involving factors such as school size, the percentage of students eligible for free/reduced lunch, and the health coordinator serving the school. Participants (schools) were not masked as is not practical or desired in this implementation study, which focuses on improving the speed, quality, and quantity of intervention delivery through different strategies, acknowledging the influence of participants' awareness on observable outcomes. The health coordinators have successfully recruited schools for previous similar studies [63, 64]. All standard implementation sites will receive RAPD following the trial portion of the study. We focus on middle school because of the heightened risk for drug use initiation during this developmental period [65].

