### Pilot study procedures

Per institutional IRB approval and to ensure ethical compliance, members of the study team and school health coordinators, including the study manager and Principal Investigator (PI), will disseminate study information to teachers, administrators, and parents at participating schools. Consistent with similar surveys in schools, we will provide parents with an opt-out option, and participant assent will be required before survey access. Students, then, will be allowed to participate in the study unless their parents explicitly choose to opt them out. Students will complete a self-administered survey with a unique identifier not linked to school or personal information. We will administer the survey through a secure online server to protect data confidentiality. As the MMH is incorporated into the school curriculum, students will complete the surveys during their health class before MMH delivery and upon course completion. For students without parental consent or those who choose not to assent, an alternative activity, such as a worksheet, will be provided to ensure their inclusion in school activities. Based on a 75% response rate, as observed in other community studies [88], we expect approximately 450 students to participate in the survey. As a study consistent with educational practices and existing school-based survey administration, there are few risks associated with participation; the primary adverse event of concern is potentially upsetting survey questions. Students who feel uncomfortable or upset by survey questions are permitted to skip questions or end participation at any time and are encouraged to report their concerns to their classroom teacher, which will then be shared with the study team. The researchers will report any adverse events to the institutional IRB.

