**Effectiveness: risk perception**			
Occasional use [drug] (1)	1 = no risk – 4 = great risk	Pre-/post-implementation	MTF^a^ [1]
Regular use [drug] (1)	1 = no risk – 4 = great risk	Pre-/post-implementation	MTF^a^ [1]

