#### Missing data

Before data collection, the team will meet to discuss plausible reasons for missing data and determine items related to those reasons to include in the quantitative survey as auxiliary variables (i.e., variables that might lead to non-random patterns of missingness but are not of interest as part of the main hypotheses) to increase the likelihood of missing data being due to MAR (missing at random) and MCAR (missing completely at random) processes. In addition to using added items to inform future handling of missingness (i.e., multiple imputation, FIML (full information maximum likelihood)), we will calculate informative principal components [102] so our handling of missing data is informed by all available data, including multivariate interactions, without adding undue burden on model estimation stemming from a large number of variables.

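### The student post-test is set by delivery of the drug use units in one section and by course completion in another; if the delivery trigger governs, classes that teach none of the units may have no post-test

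*Protocol article*

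**What the plan says.** The article gives the timing of the student post-test in three places.

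- **Student outcomes:** the post-test comes "after delivery of the drug use prevention units (post-test"). The same sentence ties the first survey to the calendar: "Student surveys will be administered at baseline (the beginning of the semester or trimester").
- **Pilot study procedures:** "students will complete the surveys during their health class before MMH delivery and upon course completion".
- **Table 2:** for risk perception and drug use, only "Pre-/post-implementation". Satisfaction and key skills are measured post-implementation only.

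Three other sections bear on the point.

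- **Fidelity: dose delivered, adherence** makes delivery an outcome, obtained by "summing the lessons covered during the drug use prevention units (17 lessons").
- **Eligibility and randomization** says that the study targets the speed, quality and quantity of delivery. It admits schools where "health teachers must report delivering less than 80% of the MMH curriculum" "and/or report two or more barriers to MMH implementation". Five schools go to each arm.
- **Missing data** names "multiple imputation, FIML (full information maximum likelihood") as ways to handle missing values, and aims for data missing at random.

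**The concern.** A measurement time should not depend on something the randomised strategy is meant to alter. Under the Student outcomes wording it does. RAPD is intended to raise the quantity and speed of delivery, and the post-test follows delivery. Two things could then differ by arm: whether a class has a post-test at all, and how long after baseline it is taken.

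If RAPD leads more classes to teach the units, the classes without a post-test would be mainly in the standard arm, and they would be the classes whose students received none of the content. The student contrast would be made among delivering classes. A later analysis plan could not recover surveys that were never given.

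Student outcomes are secondary, and the Student data section treats them as exploratory. That section also intends them to supply effect sizes, variances and implications for power, which matter for the larger trial.

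**Working it through.** There is no figure in the article to reproduce. The check compares the texts and then illustrates the possible size with assumed inputs.

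**1. Which classes reach each anchor?**

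| Class | Reaches delivery of the drug use units? | Reaches course completion? |
|---|---|---|
| Teaches all the units | Yes | Yes |
| Teaches some lessons | Unclear from the wording | Yes |
| Teaches none | No | Yes |

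The two anchors differ for the last row, and possibly for the second.

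**2. Inputs.** From the article: 17 lessons and five schools per arm. Assumed, because the article gives neither: the gain in SD units from the units, and the shares of classes delivering.

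**3. All-or-none delivery.** Let p1 and p0 be the shares of classes delivering under RAPD and standard implementation, and g1 and g0 the gains where delivered.

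- Contrast with every class surveyed = p1·g1 − p0·g0
- Contrast with only delivering classes surveyed = g1 − g0

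With p1 = 0.95, p0 = 0.75 and both gains 0.30: 0.285 − 0.225 = 0.06 SD, against 0. The share of classes without a post-test differs by 20 percentage points (5% v 25%).

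With g1 = 0.40 and g0 = 0.30: 0.380 − 0.225 = 0.155 SD, against 0.10 SD. The loss is 0.055/0.155, about 35%.

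**4. Partial delivery in every class.** Assume 0.30 SD at 17 lessons, linear in lessons. With 15 v 10 lessons the contrast is 0.30 × 5/17 = 0.088 SD. Every class has a post-test under either anchor, provided partly delivering classes are surveyed, so nothing is lost.

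**5. Mixed.** Delivering classes teach 15 (RAPD) v 11 (standard) lessons and the others teach none. With q1 and q0 the shares teaching none:

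- Every class surveyed = 0.30 × [(1 − q1)·15 − (1 − q0)·11]/17
- Delivering classes only = 0.30 × 4/17 = 0.071 SD

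| Teaching none, RAPD v standard | Every class (SD) | Delivering only (SD) | Lost |
|---|---|---|---|
| 0% v 20% | 0.109 | 0.071 | 35% |
| 10% v 40% | 0.122 | 0.071 | 42% |
| 0% v 40% | 0.148 | 0.071 | 52% |

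**6. Can the analysis repair it?** Not for classes with zero delivery. If no such class is surveyed, no post-test exists at zero dose, and imputation or full information maximum likelihood must extrapolate from classes that taught at least some lessons. On satisfaction and key skills those classes would contribute no data at all. One non-delivering school is 1/5 = 20% of an arm's clusters.

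**7. Follow-up interval.** Baseline is fixed near the start of term. If RAPD brings delivery forward, or lengthens it by adding lessons, the interval to a delivery-triggered post-test shifts in that arm. The direction cannot be told from the article.

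**The case against.** The best reply is that Pilot study procedures already puts the survey at course completion, which a class reaches however many drug use lessons it taught. On that reading nothing is lost, and the Student outcomes wording merely describes an ordinary before-and-after survey. This stands in part: the harm is conditional on which section governs. But the two sections give different anchors, and a teacher following Student outcomes has no trigger to give the post-test if the units are not taught. Reconciling them on the delivery anchor would leave the problem in place.

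A reader might infer three stronger things that the article does not support.

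- **That schools are chosen for under-delivery.** The rule is under-delivery and/or barriers, and the 80% refers to the whole curriculum. A teacher below it may still teach the drug use units. The remark under Ongoing training that teachers may not deliver some content at all concerns material outside their expertise, such as new drugs.
- **That unfinished classes are excluded.** Nothing says so. Dose is counted lesson by lesson, so partial delivery is an expected state.
- **That any RAPD effect through better delivery disappears.** Steps 3 to 5 show otherwise: only the part that works through whether the units are taught is lost.

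It can also be said that lesson dose and auxiliary variables would inform the missing-data model. They may help for partly delivering classes, but they do not supply observations at zero dose. Finally, survey logistics for skipped units may sit in a fuller protocol. The absence of such a rule is therefore not the finding; the two anchors and the nature of one of them are.

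**Conclusion.** The point holds in conditional form. The article gives two incompatible anchors for the student post-test, and one is a post-randomisation event that RAPD is designed to change. If that anchor governs and some classes teach none of the units, the missing post-tests and the follow-up interval may differ by arm, and the effect through whether the units are taught is lost from the student estimates. Dose and quality effects among delivering classes remain.

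The size is unknown. The losses shown, from none to all of the contrast, rest wholly on assumed gains and delivery rates, and on a dose effect that is linear or all-or-none. If every class teaches some of the units and is surveyed, there is no such loss. The primary outcomes of feasibility, acceptability and appropriateness are not affected. The consequence is for the exploratory effect-size and variance estimates carried to the larger trial.

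**What to change.** Give Student outcomes and Pilot study procedures the same sentence. Every enrolled class takes the post-test at one fixed point at the end of the health course or term (for example its last two weeks), whether or not and however far the drug use units were taught. Define post-implementation in Table 2 as that point. Record the lessons delivered by that date, and analyse all classes as allocated.

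The cost is a sentence in the survey schedule. The small downside is that some classes will be surveyed with little or no exposure, or some time after the units ended.

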**Effectiveness: risk perception**			
Occasional use [drug] (1)	1 = no risk – 4 = great risk	Pre-/post-implementation	MTF^a^ [1]
Regular use [drug] (1)	1 = no risk – 4 = great risk	Pre-/post-implementation	MTF^a^ [1]
**Implementation outcomes: fidelity engagement**			
Satisfaction (4)	5-point Likert	Post-implementation	Giles et al. [93] adapted
Key skills: assertive communication, refusal skills, decision-making (9)	5-point Likert	Post-implementation	National Health Educ Standards [16], MMH [94]
**Effectiveness: drug use behaviors**			
Drug use (vaping, cannabis, alcohol, prescription medications) (16)	1 = none 7 = 40 or more times	Pre-/post-implementation	MTF^a^ adapted [1]
**Disparities: measures of socioeconomic disadvantage**			
Economic disadvantage: food insecurity (9), free/reduced lunch (1)	Insecurity: 1 = a lot to 3 = never; eligibility: yes, no	Pre-implementation	US Food Security Survey Module [95]

^a^Monitoring the Future

### Data analytic approach: primary outcomes

#### Qualitative data

We will use an inductive/deductive thematic analytical approach outlined by Hsieh and Shannon for interview transcripts [96]. First, the study staff and the PI will review the transcript material to develop a broad understanding of the content related to the project’s specific aims. We then will identify topics of discussion and observation. During this and subsequent steps, we will document initial impressions of topics and themes and their relationships to each other to define the boundaries of specific codes [56]. Second, project team members will independently code the interview empirical material to condense the data into analyzable units. Segments of text ranging from a phrase to several paragraphs will be assigned codes based on a priori or emergent themes, also known as open coding [97]. We will assign codes to describe connections between categories and between categories and subcategories, that is, axial coding [97]. We will match lists of codes developed by each investigator and integrate them into a single codebook. Third, two staff will independently code text. We will resolve disagreements through discussion between investigators to create an enhanced definition of codes, resulting in a final codebook. Using this codebook, two study team members will separately review transcripts to determine the level of agreement in the codes applied. A level of agreement greater than 80% indicates good reliability in qualitative research [98]. Fourth, based on these codes, we will use the computer program QSR NVivo [99] to generate a series of categories connecting text segments grouped into separate “nodes.” We will use these nodes and node structures to further the process of axial coding to examine the association between different a priori and emergent categories. Fifth, by continually comparing these categories, we will condense the distinct categories into broad themes.

#### Quantitative data

We will characterize the primary outcomes of feasibility, acceptability, and appropriateness of the RAPD strategies using means and 95% confidence intervals, medians, and interquartile ranges or counts and percentages as appropriate.

#### Mixed method data integration

To integrate both quantitative and qualitative data effectively, we will follow the steps outlined by Creswell and Plano Clark [100]. These steps will enable us to derive meta-inferences, that is, insight beyond each data strand alone when combining data from both sources [96]. We will utilize a spiraled comparison approach, engaging in a continuous iterative process of analyzing and comparing the quantitative and qualitative data strands. This iterative analysis will involve moving back and forth between the two data types, cyclically considering their respective results to merge and enrich our findings [100]. This iterative process will help us identify areas of convergence, divergence, and expansion, ultimately allowing us to develop interpretations or meta-inferences [100] that address our research questions concerning the feasibility, acceptability, and appropriateness of RAPD. To ensure the validity of our interpretations, we will utilize other data sources (e.g., notes from health coordinator facilitation meetings) to develop a comprehensive understanding of the phenomena under investigation, testing the robustness of our findings [101]. Additionally, we will engage in member checking, involving partners, including MDHHS and Michigan School Health Coordinators Association, to review our results following data analysis. This collaborative process will help us validate our interpretations and ensure alignment with the perspectives and experiences of key partners. Any discrepancies that arise during the analysis process will be addressed through methods such as re-analysis of the existing data or, if necessary, by collecting additional data [100]. This approach will allow us to resolve inconsistencies and enhance our study’s overall rigor and validity.

Guided by Pearson et al. [52], we will employ a mixedmethod approach using quantitative and qualitative criteria, along with a “traffic light” system (red, yellow, green), to assess a priori progression to a larger-scale trial. For Aim 2 feasibility outcomes (recruitment, retention, data collection procedures and measures, and feasibility), “green” indicates meeting all pre-defined feasibility targets, “yellow” signifies meeting some targets with potential modifications, and “red” indicates unmet targets requiring substantial revisions.

### Data analysis: secondary outcomes

#### Teacher data

Consistent with Aim 2 primary outcomes, we will analyze the teacher-focused secondary quantitative outcomes (e.g., fidelity) using means and 95% confidence intervals, medians, and interquartile ranges or counts and percentages as appropriate.

#### Student data

Aim 2 analyses of student survey data will focus on estimates of effect size, variance, implications for statistical power, and exploring potential differences between the RAPD implementation strategy and standard implementation on student perceptions of risk, attitudes, behaviors, and MMH engagement. Given the study design, we will utilize mixed-factorial statistical analyses to characterize the magnitude of differences of the pre-/post changes in measures of risk, attitudes, beliefs, and other student-level outcomes. Each model will utilize random Y-intercepts to accommodate the repeated observations within student and school, and fixed-effects parameters comparing time (pre-/post changes), group (RAPD, standard implementation difference), sex/gender, socioeconomic status, and their interaction (as appropriate given sample size constraints). We will employ mixed-factorial regression models for outcomes assumed to follow a normal distribution, logistic regression for dichotomous outcomes, or ordinal regression for outcomes ordinal in scale. The analyses will use Satterthwaite corrections for degrees of freedom.

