### Aim 2: design and pilot test RAPD deployment

#### Sample and setting

This pilot study, testing the set of implementation strategies designed based on Aim 1 results, will include ten middle schools from regions across the state (urban, rural, suburban) served by participating health coordinators. We anticipate 24 students per school, consistent with the mean number of students per classroom in Michigan [59]. The health coordinators’ service regions include one or more adjacent counties. We will enroll one or more health teachers from each participating school. Students aged 12–14 who are enrolled in the participating teacher’s classroom are eligible to participate in a pre- and post-implementation survey.

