#### Sample size

Our proposed sample size includes 10 clusters with an average cluster size of 32 participants, consistent with the range reported in pilot cluster randomized controlled trials (inter-quartile range: 4–16 clusters; cluster size: 14–82) [60]. This sample size is appropriate for a pilot study designed to assess the feasibility and acceptability of implementing the intervention at the school level as primary and to estimate the variability in key implementation outcomes such as fidelity and student outcomes as secondary. This sample size also reflects the available resources for the pilot study while still allowing for meaningful data collection.

The justification for this sample size aligns with best practices for pilot studies, which prioritize achieving sufficient precision for key implementation parameters rather than powering analyses for statistical significance [52]. Given the exploratory nature of pilot studies, formal power calculations are not required, as the primary aim is to assess feasibility, variability, and implementation processes [61]. To ensure that our pilot sample will allow us to draw reasonable conclusions for the parameter estimates in a larger study, we conducted an AIPE (Accuracy in Parameter Estimation) analysis. We found that across 1000 simulations, the average 95% confidence interval widths for the student outcomes were 0.18 standardized units, and 0.85 for school-level variability. The focus on AIPE is more central to our aim in this pilot study than statistical power, especially for the school-level effects. Thus, our proposed sample size reflects a balance between the pragmatic constraints of a pilot trial and the need to collect adequate data to inform the design and conduct of subsequent larger-scale effectiveness trials.

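### The student model estimates the RAPD effect as a raw difference of pre/post changes, which over-corrects chance baseline differences between five schools per arm; a common-baseline longitudinal model avoids most of this

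*Protocol article*

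**What the plan says.** The Student data section of the protocol article sets the target as "mixed-factorial statistical analyses to characterize the magnitude of differences of the pre-/post changes in measures of risk", along with attitudes, beliefs and other student outcomes. Both surveys enter as outcomes: "Each model will utilize random Y-intercepts to accommodate the repeated observations within student and school". The fixed part is "fixed-effects parameters comparing time (pre-/post changes), group (RAPD, standard implementation difference), sex/gender, socioeconomic status, and their interaction (as appropriate given sample size constraints"). No baseline covariate, common baseline mean or school-by-time random effect is named. The same section says that the analyses serve to estimate effect size and variance and to inform power, and it calls the arm comparison exploratory.

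Under Student outcomes, "Student surveys will be administered at baseline (the beginning of the semester or trimester"), and again after the drug use prevention units. Table 2 lists risk perception and drug use at both surveys, and satisfaction and key skills only afterwards. Under Eligibility and randomization, "Five of the matched sites will be randomized to the RAPD and five to standard implementation". Matching uses factors such as school size, free/reduced lunch and health coordinator. The Sample size section assumes "10 clusters with an average cluster size of 32 participants"; the Sample and setting section says "We anticipate 24 students per school".

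**The concern.** With time, a free group effect and their interaction, the time-by-group coefficient in complete data is simply the arm difference in mean change. One fit of the planned structure to simulated complete data confirmed this: the coefficient and the raw difference of mean changes were both -0.1308. The coefficient on baseline is in effect fixed at 1.

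Because schools are randomised, a baseline difference between arms is chance. The post-test is expected to carry forward only part of it, so subtracting all of it pushes the estimated RAPD effect in the opposite direction. With five schools per arm, such differences need not be small. Matching on school characteristics may reduce them, but it does not balance baseline risk perception or drug use directly.

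What is at stake is the quality of the effect size and variance carried into the larger trial. Validity of the comparison over randomisation is not in question.

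**Working it through.** **Inputs from the article.** 10 schools, 5 per arm; m = 32 students per school; a difference-of-changes target.

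**Assumed, because the article gives none of them.** ICC 0.01 to 0.10; CAC (correlation of a school's effect between the two surveys) 0.5 to 1; ρ (within-school pre/post correlation of a student's score) 0.3 to 0.7. The outcome is linear with total variance 1 at each survey, and matching is ignored.

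**The article's own precision figure.** The Sample size section reports a mean 95% interval width of 0.18 standardised units for student outcomes, without the parameter or the inputs.
- Read as a difference of changes with 320 students and no clustering, width = 2 × 1.96 × √[(4/320) × 2(1−ρ)], and 0.18 needs ρ of about 0.92.
- Read as a pooled time effect, width = 2 × 1.96 × √[2(1−ρ)/320], and 0.18 needs ρ of about 0.66.

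The figure can be neither reproduced nor refuted, and nothing below relies on it.

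**Step 1: the right share of the baseline difference.** For school means:
- variance v = ICC + (1−ICC)/m
- pre/post covariance c = ICC × CAC + (1−ICC)ρ/m
- r = c/v

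At ICC 0.05, CAC 0.8, ρ 0.5: v = 0.05 + 0.95/32 = 0.0797; c = 0.04 + 0.0148 = 0.0548; r = 0.69. The change contrast subtracts 1 where 0.69 is right, so its slope on the chance baseline difference is −(1 − 0.69) = −0.31.

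The chance SD of the baseline arm difference is √(2/5 × 0.0797) = 0.179. A one-SD difference therefore moves the change contrast by (1 − r) × 0.179:
- 0.09 SD at CAC 0.5 (r = 0.50)
- 0.06 SD at CAC 0.8 (r = 0.69)
- 0.03 SD at CAC 1 (r = 0.81)

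**Step 2: standard errors.** Each is √(2/5 × school-level variance):
- change: 2v(1−r)
- best baseline-adjusted contrast: v(1−r²)
- adjustment for the student's own baseline only: ICC(1+ρ²−2ρCAC) + (1−ICC)(1−ρ²)/m

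| ICC | CAC | ρ | r | change | best adjusted | student baseline only |
|---|---|---|---|---|---|---|
| 0.02 | 0.5 | 0.5 | 0.50 | 0.142 | 0.123 | 0.123 |
| 0.02 | 0.8 | 0.5 | 0.62 | 0.124 | 0.112 | 0.113 |
| 0.05 | 0.5 | 0.5 | 0.50 | 0.179 | 0.155 | 0.155 |
| 0.05 | 0.8 | 0.5 | 0.69 | 0.141 | 0.130 | 0.134 |
| 0.05 | 1 | 0.5 | 0.81 | 0.109 | 0.104 | 0.118 |
| 0.10 | 1 | 0.3 | 0.85 | 0.125 | 0.121 | 0.173 |

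The ratio of best adjusted to change is √[(1+r)/2], which is below 1 whenever r is below 1. Over the assumed grid it runs from 0.82 to 0.98. Adjusting for the student's own baseline only is worse than change in the last two rows.

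**Step 3: allowing for estimated variance components.** The share r must be estimated from the same 10 schools. A simulation used a moment-based version of the common-baseline model (4,000 trials per scenario; ICC 0.01, 0.02, 0.05, 0.10; CAC 0.5, 0.8, 1; ρ 0.3, 0.5, 0.7).
- Its SE was 0.83 to 1.00 times that of the change contrast.
- Its slope on the chance baseline difference was −0.05 to +0.11, against −0.66 to −0.07 for the change contrast.

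**Sensitivity to school size.** The article also implies 24 students per school, and 450/10 = 45 from its expected survey total. At ICC 0.05, CAC 0.8, ρ 0.5 the best-case ratio is 0.91 at 24, 0.92 at 32 and 0.92 at 45. The inconsistency in school size does not change the result.

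**The case against.** The strongest reply is that both estimators are unbiased over randomisation and that their ranking depends on parameters the article does not give. The outcomes are secondary, the comparison is exploratory, formal power is disclaimed, and progression rests on feasibility targets. The planned model also yields variance components and a pre/post correlation from which a later trial could be sized. All of this stands, and it limits the weight of the point.

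A reader might infer that the remedy is to regress the post-test on each student's own baseline, and that this always gains precision. The documents do not support that. Chance imbalance arises between schools, so the relevant slope is that of school means and not the student slope. When ICC is about 0.05 or more and school effects are stable, student-level adjustment alone under-corrects (slope up to about +0.5) and is less precise, as the last two table rows show. Stable school effects are also what the planned school intercept without a school-by-time term assumes.

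The reply does not rescue the raw change contrast. Its slope on chance imbalance was negative in every scenario examined, and the common-baseline version was no less precise to two decimals, even with variance components estimated from 10 schools. Matching would shrink imbalance if the matching factors predict the outcome. By how much cannot be worked out from the article.

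**Conclusion.** The point holds as one of conditional bias and efficiency. The planned contrast subtracts too much of any chance baseline difference between arms. Under the assumed ranges, a common-baseline model has a standard error about 0 to 17% smaller. The gain is largest at low ICC or where school effects drift between surveys, and nil where schools are fully stable and the ICC is high.

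A reader might go further and infer that the planned analysis is biased or invalid, or that a definite amount of power is lost. Neither follows: the change estimator is unbiased over randomisation, and the article gives no ICC, pre/post correlation, school stability or target effect.

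The figures are for a linear outcome with balanced schools and unmatched allocation. The principle carries over to the logistic and ordinal models; the percentages may not. The common-baseline constraint also assumes that the first survey precedes any effect of RAPD on students and that allocation does not influence who takes part. The article places the first survey before MMH delivery, which fits the first assumption.

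**What to change.** For outcomes measured at both surveys (risk perception and drug use):
- Keep the longitudinal mixed model but constrain the arms to a common baseline mean: time and time-by-group, with no group main effect, plus sex/gender and socioeconomic status as planned.
- Use student and school random intercepts plus a school-by-time random effect.
- Name the time-by-group term as the RAPD effect and retain it whatever the sample size. If it were dropped, a group coefficient would average the pre and post differences.
- Report raw changes by arm as description. Post-only outcomes need a plain post-test comparison.
- Do not substitute adjustment for the student's own baseline alone without qualification. If a regression on baseline is preferred, include the school baseline mean as well, accepting that 10 schools leave few degrees of freedom.

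The cost is wording and a small change of model code, with no new data. Linked pre/post records with school membership are already needed for the planned random intercepts, and students with only one survey can stay in the model. The downsides are one more variance component estimated from 10 schools, and a result that reads as a baseline-adjusted difference instead of a difference in change.
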